### Formation of groups and blinding

The subjects will be randomly and equiprobably assigned to the experimental or the control group. The randomization will be generated by computer, with random numbers following a size 4 block system (ensures heterogeneity of the diet supplement administered in the consecutive patient groups, ensuring that in each interval exists a similar number of patients in each group). Randomisation will be done centrally.

The containers of yoghurt (with or without the plant sterol ester supplement) will be given to the patients in a blinded manner. To protect the blinding, the container of the placebo and test product will be exactly the same.

To ensure objectivity in the interpretation of the results, the study will be conducted in a blinded manner for the patients, investigators and data analysts. The placebo and the active product will be identical in appearance and will be identified by a code, the assignment of which will be unknown by the patients and the investigators.

### Intervention

The administration of a dairy product in the form of liquid yoghurt, marketed in Spain, that contains 2 g per container of plant stanol esters: sitostanol and campestanol (AHA recommended dose - 1.5 to 3 g). The enriched product and the placebo will have the same characteristics (composition and outward appearance), but the placebo will not contain stanol esters. The dose will be one container a day, after the main meal, for 24 months. The participants may continue with their previously prescribed lipid-lowering treatment and new treatment needed for this disease or for other diseases. Composition per container: proteins 1.8 g, carbohydrates 9.8 g, fat (except stanol) 1.4 g, plant stanol 2 g, vitamin B6 0.6 mg, folic acid 60 mg. The control group will receive one unit a day of yoghurt not supplemented with stanol esters that has a similar appearance to the enriched yoghurt.

### Follow-up

The subjects will be followed-up for two years.

- Selection: patients who meet the inclusion criteria will be asked to participate in the study. After giving their informed consent they will be given an appointment for the initial visit and for the analytical tests.

- Initial visit: the participant will be randomised to one of the two groups. Their medical history will be taken and they will be given a physical examination. The corresponding dairy product will be dispensed (the following doses will be dispensed according to their expiry date). At this visit a lipid-lowering diet will be recommended to all the participants.

- Follow-up visits: at 1, 3, 6, 12, 18, and 24 months, the physical examination and analytical test parameters will be recorded. The cardiovascular risk will be calculated and possible adverse effects and compliance or adherence to the food supplied will be recorded.

The study will be finalised for the patient in the following circumstances: completed follow-up period (2 years), death, violation of the protocol, adverse event, intercurrent disease that makes it impossible to ingest food and patient abandons study or withdraws consent.

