#### Secondary variables

-Change in cardiovascular risk at the follow-up visits. Systematic Coronary Risk Evaluation (SCORE) and Gerona Heart Register (REGICOR) tables will be used for the evaluation.

-Adherence to the dairy product (liquid yoghurt) by self-report and Morisky-Green scale, which determines the degree of coincidence between the patient's behaviour and the doctor's advice (a non-complier is one who answers one of the four questions of the scale inappropriately).

-Adverse events. Considered as any undesirable event in any patient included in the study, even though it does not have a causal relation with the product. Known adverse events of phytosterols in the diet at the proposed doses: occasionally mild digestive alterations.

-Adherence to the dietary recommendations: 5-point Likert scale.

-Frequency of food intake using the CDC-FFQ questionnaire, validated in Spain (Aguirre, 2008) considered appropriate to classify the subjects according to their intake of food and nutrients.

-Occurrence of cardiovascular events during the follow-up period: ischaemic heart disease, atherothrombotic cerebrovascular disease, heart failure and peripheral artery disease.

-Weight, height, body mass index (BMI): classification of subjects according to degree of obesity.

-Physical activity: amount of aerobic exercise ("active" if performs aerobic exercise for 30 minutes or more, three or more times a week, "partially active" if exercises with less frequency and for less time that this and "inactive" when does not perform any type of exercise).

-Smoking habit: considered smoker if answers yes to the question "do you smoke?"

-Systolic and diastolic blood pressure (two measurements): the result will be the mean of the two measurements.

-Health problems (WONCA ICPC-2).

-Whether taking lipid-lowering pharmacological treatment.

-Socio-demographic data: age, gender, marital status, educational level and social class based on occupation (National Classification of Occupations).

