#### Efficacy analysis

After the prior stages of data purification, exploratory analysis and categorisation or transformation of variables, the following were performed:

-Comparison of the variables of interest and the stratification and potentially confounding variables in both groups at the start of the study. Although we used a random assignment system, we checked that the baseline values of the study variables were uniform over the two groups.

-Classification of the subjects of the two groups into different LDL-cholesterol and total cholesterol reduction levels. A baseline raw analysis will be performed to evaluate the following parameters and their 95% confidence intervals: ABI (absolute benefit increase), RBI (relative benefit increase) and NNT (number needed to treat). A stratified analysis will be performed adjusted for each independent variable.

-The incidence of the endpoint variables in the two groups will be described and compared at each follow-up period (comparison of means using Student's t tests or Mann-Witney U test, depending on the distribution of the variables). The Friedman test will be used to compare the changes in lipid profile throughout the study in each of the groups.

-The effect of the dairy product on total cholesterol and LDL-cholesterol levels will be determined, adjusted for changes in adherence to the prescribed regimen (linear models generalised for repeated means).

-The convergent validity of the capillary blood measurements compared to the plasma measurements will be analysed through intraclass correlation.

The analysis will be an intention to treat analysis including all randomised patients in the efficacy analysis, according to their group and regardless of the treatment received. A per-protocol analysis will also be performed for the primary variables. Intermediate analyses will be performed to decide if the study should be prematurely terminated in the event of frequent adverse effects or a clear improvement in the test group (see Figure 1 for the study flow chart).

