## Discussion

The results of this study will provide valuable information on the efficacy of plant sterol ester supplements in preventing cardiovascular disease by lowering plasma cholesterol levels and consequently cardiovascular risk. If this supplement were effective a sounder recommendation for the consumption of plant sterols in subjects with hypercholesterolaemia could be made.

Possible limitations of the study - using a randomisation procedure reduces the risk of selection bias as the investigator will not assign treatment and any factor that effects participation will be balanced in the two groups. Confounding will also be reduced as randomisation tends to divide the determinant factors, which influence the final result, equally between the two groups. However, bias could exist on collecting information due to the regression towards the mean effect or tendency of the continuous variables towards the mean in successive measurements, applicable to the analytical results. There is also a possible risk of differential loss to follow up between the two groups, due to the length of the study and also to the placebo effect which could contribute to the patients abandoning the study because they consider that the treatment provided is not having any effect.

The study protocol has been evaluated and approved by the Institutional Review Board of the Albacete Health Area on 23rd April, 2009. During the performance of the study the following ethical principles will be respected: voluntary participation with consent of the patient, guarantee of anonymity in the information provided by the patient, data provided by the patient exclusively restricted to use in the proposed study. The investigators will ensure that the study is conducted in accordance with the declaration of Helsinki and with legislation in effect (Royal Decree 223/2004) and the New Code of Medical Ethics of the Spanish Medical Association. The study will fully comply with Good Clinical Practice principles.

Finally, for the development of this project the following principles have been considered: 1) data on the dairy product are sufficient to guarantee that the risk to the study participants is acceptable; 2) the objectives of the study will probably provide further knowledge of the topic to be studied; 3) the available information warrants the performance of this study and its potential risk to the participants.

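### Follow-up ends for a patient on a protocol violation, adverse event or intercurrent disease, so later lipid values that the planned intention-to-treat analysis needs would not be collected

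*Protocol article*

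**What the plan says.** The Follow-up section of the protocol article sets visits at 1, 3, 6, 12, 18 and 24 months. It then lists what ends participation, opening with "The study will be finalised for the patient in the following circumstances". The list reads "completed follow-up period (2 years), death, violation of the protocol, adverse event, intercurrent disease that makes it impossible to ingest food", followed by abandonment or withdrawal of consent. What ends is the study, and no visit or blood sample after stopping is described.

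The Efficacy analysis section says: "The analysis will be an intention to treat analysis including all randomised patients in the efficacy analysis", and continues "according to their group and regardless of the treatment received". It adds: "A per-protocol analysis will also be performed for the primary variables".

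The Secondary variables section defines an adverse event broadly: "Considered as any undesirable event in any patient included in the study, even though it does not have a causal relation with the product". The Follow-up list adds no condition on severity or relatedness.

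The Discussion names attrition as a limitation: "There is also a possible risk of differential loss to follow up between the two groups".

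**The concern.** An intention-to-treat comparison differs from an on-treatment one through the outcomes of patients who stopped or departed from their assigned product. If measurement stops when the patient stops, those outcomes do not exist for the remaining visits. This is a rule about data collection stated in the protocol. A missing-data method in an analysis plan could model the absent values but could not recover them.

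What is at stake is the later part of the primary variable, the change in lipid profile out to 24 months. Patients absent from those visits would be absent because of events after randomisation, which may occur at different rates or in different kinds of patient in the two arms. Randomisation would no longer fully protect the comparison at those visits.

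**Working it through.** **Step 1. The two rules side by side.** Take a patient closed out for an adverse event at month 9.

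- Under Follow-up, baseline and months 1, 3 and 6 are recorded; months 12, 18 and 24 are not.
- Under Efficacy analysis, this patient belongs in the comparison at every visit, in the assigned group.
- Both can be met up to month 6. From month 12 they cannot both be met with observed data.

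**Step 2. What each planned analysis does with this patient.**

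- Student's t or Mann-Whitney test at each visit: included to month 6, absent afterwards.
- Friedman test within each group: it needs a value at every time point, so the patient drops out altogether.
- Repeated-measures model for total and LDL-cholesterol: it can use the partial series. Its later estimates then rest on an assumption about the unobserved values. It is also adjusted for changes in adherence, a post-randomisation variable, so it does not directly give the intention-to-treat effect.

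**Step 3. The planned effect and sample size.** From the Sample size section: mean LDL-cholesterol 157 mg/dl, SD 30, reduction 10%, two-sided alpha 0.05, power 90%, 76 per group, 20% loss, 182 in total.

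- Effect: 0.10 × 157 = 15.7 mg/dl.
- n per group = 2 × (1.960 + 1.282)² × 30² / 15.7² = 76.7, so 77. The stated 76 gives 89.7% power. The plan's figure is reproduced to within rounding.

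**Step 4. Illustration of size.** The document gives no rate of stopping for these reasons, so f below is an assumption. Suppose a fraction f of the active arm stops, stoppers lose all effect, and stoppers otherwise resemble the rest.

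- Intention-to-treat difference = 15.7 × (1 − f).
- Difference among those retained = 15.7.
- Overstatement = 1 / (1 − f) − 1.
- Power if everyone is measured = Φ(difference / (30 × √(2/91)) − 1.960), with 182 / 2 = 91 per arm.

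| f (assumed) | ITT difference (mg/dl) | Retained patients (mg/dl) | Overstatement | Power for ITT difference, 91 per arm |
|---|---|---|---|---|
| 10% | 14.1 | 15.7 | 11% | 88.8% |
| 20% | 12.6 | 15.7 | 25% | 80.6% |
| 30% | 11.0 | 15.7 | 43% | 69.5% |

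These figures apply only to visits after stopping. If stoppers differ from the others in prognosis, a further bias of either sign is added.

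**The case against.** The strongest reply is that the Follow-up list is a condensed list of recognised reasons for ending participation, not an automatic trigger. Read literally with the broad adverse event definition, it would close out so many patients over 24 months that the assumed 20% loss would make little sense. The plan also records adverse effects at follow-up visits and tracks cardiovascular events during follow-up. Both fit poorly with ending observation at the first undesirable event. This stands as far as it goes: the article does not say that every event leads to withdrawal. It does not remove the conflict, because whoever is closed out for one of these reasons has no later measurement described.

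A reader might draw four stronger conclusions, none of which the document supports.

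- That an intention-to-treat analysis cannot be done, or that only completers have data. Visits before stopping remain analysable by assigned group.
- That the intention-to-treat and per-protocol sets would be nearly identical. The article does not define a violation or say that it includes not taking the yoghurt. Adherence is recorded at follow-up, a category of non-complier is defined, and an analysis adjusts for changes in adherence. All this suggests that non-adherent patients stay in.
- That the Discussion confirms the problem. It attributes differential loss to the length of the study and to patients leaving because they see no effect. That is voluntary withdrawal, not closure under the protocol.
- That the effect will be overstated by 11% or 25%. The 10% rate is assumed, and the plan's 20% is loss from any cause.

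Handling of missing data may sit in a fuller protocol or analysis plan that is not shown, and its absence from the article is not criticised here.

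**Conclusion.** The point holds in a limited form. The Follow-up and Efficacy analysis sections contradict each other for visits after a patient is closed out on a protocol violation, adverse event or intercurrent disease. Followed as written, lipid values at those visits, most of all month 24, are never collected, and the later comparisons lean towards patients who remained on protocol.

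The size and direction of the resulting bias cannot be determined from the document. The differences of 14.1 and 12.6 mg/dl against 15.7 show only what would follow from 10% or 20% stopping in the active arm with complete loss of effect. The conflict itself rests on the stated wording and needs no numerical assumption. It merits correction because measurements missed during follow-up cannot be obtained afterwards.

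**What to change.** Reconcile the two sections by separating two events that the Follow-up section treats as one: stopping the study product and ending follow-up.

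- For patients who stop the product after a protocol violation, adverse event or intercurrent disease and who still consent, keep the lipid measurements already scheduled, to month 24.
- Include those values in the intention-to-treat analysis under the assigned group.
- Let follow-up end at completion of 24 months, death or withdrawal of consent.
- Leave unchanged when the product itself is stopped.

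The cost is a short amendment and attendance at visits that are already planned. Some patients who stop will decline further visits. Loss through voluntary withdrawal, which is the loss the Discussion describes, remains. If stoppers do lose the effect, the difference being estimated is smaller and power for it is lower, as the illustration shows. That smaller difference is nevertheless the one the stated intention-to-treat analysis is meant to estimate.

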### Primary variables and measuring methods

#### Primary variable

-Change in lipid profile at 1, 3, 6, 12, 18 and 24 months. Lipid levels will be measured in both plasma and capillary blood at the initial visit. The validity of the capillary blood lipid levels can be checked with the Cardiochek analyser (by total cholesterol, HDL-cholesterol and triglyceride strips, and subsequent calculation of LDL-cholesterol using the Friedewald formula). The measurements at 3, 12 and 24 months will be in plasma. At 1, 6 and 18 months they will only be in capillary blood.

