### Sample size

To obtain a 90% statistical power with an alpha error of 0.05 (bilateral hypothesis). The effect to be demonstrated is based on the following:

- The expected mean value of LDL-cholesterol in the patients included in the study is 157 mg/dl ± 30 SD (value obtained in previous studies conducted in a Spanish population).

- To demonstrate an effect of a 10% reduction in LDL-cholesterol in patients who receive the supplements, 152 subjects are needed (76 in the active group and 76 in the placebo group).

Assuming a 20% loss to follow up, 182 subjects will need to be selected and will be distributed equally between the two groups in order to obtain the maximum statistical power.

The recruitment period will be from January 2010 to September 2010.

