### Statistical analysis

#### Test of the hypothesis

The null hypothesis establishes that there is no relationship between the decrease in blood LDL-cholesterol levels and the consumption of stanol ester enriched liquid yoghurt. The alternative hypothesis establishes a relationship between such consumption and the incidence of the primary variable.

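### The primary variable is the whole lipid profile at six visits, but the hypothesis and sample size concern one LDL comparison, and no visit is named as decisive

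*Protocol article*

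**What the plan says.** The Primary variable section (and the abstract) gives the primary variable as "Change in lipid profile at 1, 3, 6, 12, 18 and 24 months". It singles out no lipid and no visit. It also says that lipids are measured in plasma at 3, 12 and 24 months, and only in capillary blood at 1, 6 and 18 months.

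The Efficacy analysis section states: "The incidence of the endpoint variables in the two groups will be described and compared at each follow-up period". The comparison is of means, by t test or Mann-Whitney test. The section gives no lead visit.

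Three other places are narrower:

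- **Study objectives:** the general objective is LDL lowering, with no time point. The first specific objective is to quantify the LDL effect at each of the six visits.
- **Sample size:** "To demonstrate an effect of a 10% reduction in LDL-cholesterol in patients who receive the supplements, 152 subjects are needed". These are split equally, 76 per arm, for 90% power at two-sided 0.05. This is one LDL difference with no visit attached.
- **Test of the hypothesis:** the null concerns LDL only. The alternative then refers back to the primary variable: "The alternative hypothesis establishes a relationship between such consumption and the incidence of the primary variable". By the article's own definition that is the whole lipid profile, so null and alternative do not describe the same quantity.

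**The concern.** A primary endpoint has to say what quantity, measured when, decides whether the trial succeeded. Here the sections disagree on the quantity and none gives the time. With six between-arm LDL comparisons and one overall error rate in mind, the 5% in the sample size section no longer describes the chance of a false claim of efficacy. If the visits disagree, for example an early difference that has gone by 24 months, nothing in the article says which result governs. The visits are not interchangeable either, since three are capillary and three are plasma. The Background justifies the trial by the short follow-up of earlier studies and sets two years for this one, so the choice of visit bears on its central question.

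**Working it through.** **1. Is the stated sample size a single-test figure?** Inputs from the Sample size section: mean LDL 157 mg/dl, SD 30, a 10% reduction, two-sided alpha 0.05, power 90%. The SD of 30 is taken at face value as the SD of the compared quantity.

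- Difference: 0.10 × 157 = 15.7 mg/dl.
- n per arm = 2 × 30² × (1.960 + 1.282)² / 15.7² = 1800 × 10.507 / 246.49 = 76.7.

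The article states 76 per arm, 152 in total. Rounding up gives 77 and 154, and the power with 76 per arm is 89.7%. A one-sided test would need 63. The stated figure is therefore a single LDL comparison at two-sided 0.05, with no allowance for more tests.

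**2. Six LDL tests at 0.05 each.** The Efficacy analysis section gives no per-test level. The 0.05 is carried over from the sample size section because it is the only level in the article.

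- If the visits were independent: 1 − 0.95⁶ = 1 − 0.735 = 0.265.
- Repeated LDL values in the same people are correlated, and the article gives no correlation, so a range is assumed. In a simulation, 200,000 sets of six standard normal statistics with common correlation r were drawn under no effect, and sets with any |Z| > 1.96 were counted.

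| Assumed between-visit correlation | Chance of at least one p < 0.05 |
|---|---|
| 0 | 26% |
| 0.3 | 24% |
| 0.5 | 21% |
| 0.7 | 16% |
| 0.8 | 14% |
| 0.9 | 11% |

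Even at 0.9 the rate is more than twice 5%.

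**3. If total cholesterol also counts as primary.** There are then twelve tests. With an assumed LDL–total cholesterol correlation of 0.9, the same simulation gives 32% at between-visit correlation 0.3, 28% at 0.5, 19% at 0.8 and 15% at 0.9.

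**4. What the alternatives cost.**

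- One named comparison: alpha stays at 0.05 and the figure in step 1 applies.
- Six LDL visits with Bonferroni: 0.05 / 6 = 0.0083 per test. This needs 113 per arm (226 evaluable) for 90% power per test; 76 per arm gives 72%.

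The article also plans interim analyses that may stop the trial for clear benefit. These are not counted above.

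**The case against.** The strongest reply is that LDL is plainly the intended variable and that testing order and multiplicity belong in an analysis plan that is not shown. The first half is largely right: objective, null and sample size all say LDL. It does not supply the visit, and it does not remove the conflict with the primary variable section. On the second half, the lack of a multiplicity procedure is not held against the article. The choice of primary variable is a protocol matter, and the article makes it inconsistently.

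A second reply is that the repeated-measures model for LDL and total cholesterol could give one overall answer. It could, but it is presented as an analysis adjusted for changes in adherence and is not named as the primary test. A third is that the objective at each visit is to quantify, which suits visit-by-visit estimation. That is fair, and it supports treating the visits as descriptive once one comparison is named.

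Some stronger readings are tempting but not supported:

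- A reader might infer that any significant lipid at any visit would count as success, giving 24 tests and a false-positive chance far above the LDL-only figures. The only null hypothesis concerns LDL, so an HDL or triglyceride result could not reject it. The four lipids are listed in a parenthesis about checking the capillary analyser, not in a definition of the endpoint. The Background also reports that no effect on HDL or triglycerides was found.
- A reader might take it as stated that each visit is tested at 5%. That is an inference.
- A reader might object that the hypotheses speak of consumption and of incidence. The efficacy section analyses all randomised patients by allocated group and compares means, which largely answers both points.

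**Conclusion.** The point holds in this form: the primary variable section disagrees with the objective, null hypothesis and sample size on which lipid is primary, and no section fixes the deciding visit. On the narrow LDL-only reading, the chance of at least one false positive is about 11% to 24% instead of 5%, and 26% is the figure under independence. This rests on two assumptions: 0.05 is applied at each visit, and between-visit correlations lie between 0.9 and 0.3. Counting total cholesterol as primary raises the range to about 15% to 32%, with the further assumption of a 0.9 correlation between the two lipids. The sample size reproduces, to within rounding, as a single-test figure and is not itself at fault on this point.

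**What to change.** Bring the primary variable section into line with the sample size and hypothesis sections by naming one primary comparison: the between-arm difference in LDL-cholesterol change from baseline, by assigned group, at one stated visit, two-sided 0.05. The 24-month plasma measurement fits the two-year rationale in the Background. It is not the only acceptable choice, and a single pre-specified summary over visits would also give one test.

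Make the other lipids, the other visits and the cholesterol-reduction classes secondary, reported as estimates with 95% confidence intervals. State the alternative hypothesis for the same LDL quantity as the null.

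The cost is wording only. No new measurements are needed, and the single-comparison basis of the 152 evaluable subjects stands. The small downside is that other lipids and visits can no longer carry the efficacy claim.
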